## Abstract

**Background:**

Although highly active antiretroviral therapy (HAART) has dramatically decreased HIV-related morbidity and mortality, the associated costs, toxicities, and resistance risks make the potential delay of HAART initiation an attractive goal. Suppression of herpes simplex virus type 2 (HSV-2) may be a novel strategy for achieving this goal because HSV-2 is associated with clinically significant increases in HIV viral load, the primary driver of HIV disease progression.

**Methods/Design:**

The VALacyclovir In Delaying Antiretroviral Treatment Entry (VALIDATE) trial is a multicentre, randomized, fully blinded, clinical trial of twice daily valacyclovir 500 mg versus placebo for delaying the need for initiating HAART among HIV-1, HSV-2 co-infected HAART-naïve adults. 480 participants from Canada, Brazil and Argentina will undergo quarterly clinical follow-up until reaching the composite primary endpoint of having a CD4+ T-cell count ≤ 350 cells/mm^3 ^or initiation of HAART for any reason, whichever occurs first. The primary analysis will use a proportional hazards model, stratified by site, to estimate the relative risk of progression to this endpoint associated with valacyclovir. Secondary analyses will compare the rates of change in CD4 count, median log_10 _HIV viral load, drug-related adverse events, frequency of HSV reactivations, rate of acyclovir-resistant HSV, and quality of life between study arms.

**Discussion:**

Although HIV treatment guidelines continue to evolve, with some authorities recommending earlier HAART among asymptomatic individuals, the potential delay of HAART remains a clinically relevant goal for many. If shown to be of benefit, implementation of the VALIDATE intervention will require careful consideration of both individual patient-level and public health implications.

**Trial Registration:**

Current Controlled Trials ISRCTN66756285

ClinicalTrials.gov NCT00860977

## Background

Highly active antiretroviral therapy (HAART) has dramatically reduced morbidity and mortality related to HIV-1 infection (herein referred to as 'HIV'), transforming an invariably fatal disease into a manageable, chronic condition. Although debate continues as to the advantages and disadvantages of earlier HAART initiation, the cost, potential long and short-term toxicities, and risk of developing drug-resistant HIV associated with daily, lifelong HAART would make the delay of HAART initiation an attractive goal for many patients. Suppression of herpes simplex virus (HSV)-2 co-infection may provide a novel therapeutic strategy for achieving this goal. The VALacyclovir In Delaying Antiretroviral Treatment Entry (VALIDATE) trial has been designed to address this question.

Recommendations for initiating HAART are based on the natural history of HIV infection and clinical trials of HIV therapy. After acute infection there is an initial profound drop in the CD4-positive T lymphocyte count from levels of > 1000 cells/mm^3 ^to roughly 700 cells/mm^3 ^six months later[1]. Patients then enter a generally asymptomatic period characterized by a steady CD4 count decline of about 50-60 cells/mm^3 ^per year, although this varies according to the HIV RNA viral load set point[2-5]. The risk of opportunistic infection and mortality rises sharply at CD4 counts ≤ 200 cells/mm^3^. Current guidelines therefore agree that HAART is warranted when the CD4 count falls to 350 cells/mm^3 ^in asymptomatic, non-pregnant adults; debate continues on the role of earlier treatment initiation, with some but not all guidelines recommending treatment at a threshold of 500 cells/mm^3 ^[6-9]. Once HAART is initiated, treatment must be lifelong, because HIV cannot be eradicated, and because treatment interruptions are associated with increased rates of HIV-associated and non-HIV-associated conditions[10].

HSV-2 is among the most common co-infections in HIV, with a prevalence of 52-95%,[11-16] and several important interactions have been observed between these two viruses. First, HSV-2 is associated with increased HIV acquisition and transmission, even in asymptomatic individuals[17-27]. Recent trials of daily acyclovir for HSV-2 suppression, however, did not show a benefit on decreasing HIV acquisition or transmission[28-30]. Persistence of HIV target cells in the genital tract, suboptimal dosing and inadequate adherence may have contributed to the negative results[31]. Second, both symptomatic, clinical recurrences of HSV-2, and asymptomatic shedding of HSV-2 have been clearly associated with increased HIV levels in both genital secretions and plasma[32-35]. Upregulation of HIV replication by HSV gene products such as infected cell protein (ICP)-0, ICP-4, ICP-27 and Us11, and stimulation of the NF-Kappa B pathway may contribute to these increases in HIV viral load[36-40]. Further, clinical trials using both acyclovir and valacyclovir suppressive therapy in co-infected individuals, including 20 men who have sex with men (MSM) in Peru, 140 women in Burkina Faso, and 67 women in Thailand have demonstrated clinically significant, reciprocal decreases in HIV RNA viral load of 0.33-0.53 log_10_[41-43].

The plasma HIV viral load, in turn, is the major predictor of CD4 cell decline and HIV disease progression, and viral load strata that increase by about 0.5 log copies/mL correlate with increased rates of CD4 decline of roughly 10 cells/mm^3^/year[2-5]. It follows, then, that HSV-2 suppressive therapy might delay HIV disease progression in HAART-untreated individuals through its effects on the HIV viral load. Indeed, a meta-analysis from the pre-HAART era suggested that > 3200 mg per day of acyclovir offered a significant survival benefit (incidence rate ratio for mortality, 0.81, 95%CI 0.68-0.96), although this effect was largely related to treatment of active herpesvirus disease in individuals with late-stage HIV/AIDS[44]. More recently, the multicentre Partners in Prevention trial from Sub-Saharan Africa has shown that acyclovir 400 mg twice daily was associated with moderately decreased progression to the composite endpoint of CD4 < 200 cells/mm3, HAART initiation, or non-trauma related death (hazard ratio = 0.84, 95%CI 0.71-0.98)[45].

These results bolster interest in the VALIDATE trial, which is addressing related but complementary issues. First, given the conduct of the Partners trial in resource-limited settings, it remains important to study the impact of HSV-2 suppression in co-infected patients from industrialized and middle-income countries. The endpoint of the Partners trial represented a stage of disease that can be avoided in settings where the standard of care is to offer HAART earlier; it is encouraging, therefore, that an exploratory analysis from the Partners trial demonstrated a delay in achieving CD4 < 350 cells/mm^3 ^from acyclovir as well (HR = 0.81, 95%CI 0.71-0.93, p = 0.002). Further, rates of CD4 count decline may be different in Sub-Saharan Africa due to the effects of nutritional status, heightened levels of immune activation (for example, as a result of co- or intercurrent infections), and HIV clade[46-49]. The predominant clades in Sub-Saharan Africa (A, D and C) differ from those in most industrialized countries (B and some others) and in South America (B but some F, C and recombinants)[50,51]. In addition, it should be noted that disease progression was a secondary endpoint of the Partners trial, which was primarily designed to study the impact of HSV-2 suppression on HIV transmission. Finally, VALIDATE is employing valacyclovir instead of acyclovir for HSV-2 suppression, and the dose of 500 mg twice daily has been demonstrated to achieve excellent herpes suppression in clinical trials of HIV, HSV-2 co-infected adults[41,42]. Valacyclovir is the pro-drug of acyclovir, and may offer advantages over acyclovir owing to an improved bioavailability (54.5% versus 15-30%) and lower pill burden[52].

Chronic suppressive therapy with valacyclovir is safe, well-tolerated and already in widespread use to prevent HSV outbreaks in those with frequent (five times a year or more) clinical reactivation. However, up to 90% of individuals with HSV-2 infection do not have any symptoms at all[53]. If HIV co-infected, such individuals may benefit from HSV-2 suppressive therapy not only through its effects on reducing herpes transmission and herpes reactivation, [54-56] but also through its salutary effects on HIV. The purpose of this multicentre, randomized, placebo-controlled clinical trial is therefore to answer the question, "Among adults co-infected with HIV and HSV-2 who are not using chronic suppressive anti-HSV therapy and who are neither currently using nor deemed to require HAART, can oral valacyclovir 500 mg twice daily delay the time until the need for HAART initiation?"

## Methods

### Study Design

The VALIDATE study is a multicentre, randomized, placebo-controlled, fully blinded, clinical trial of twice daily oral valacyclovir 500 mg versus placebo with the goal of delaying the need for initiating HAART among HIV, HSV-2 co-infected individuals who neither use nor require HAART, and who have not used chronic suppressive anti-HSV therapy for at least the 6 months prior to study initiation.

### Study Objectives

The primary objective of this trial is to compare the time from enrolment to the primary endpoint of either a CD4 cell count ≤ 350 cells/mm^3 ^measured on two consecutive occasions at least 1 month apart, or initiation of HAART for any reason, between adults with both stable untreated HIV and HSV-2 co-infection who are randomized to valacyclovir compared to those randomized to placebo.

Secondary objectives are as follows:

• To compare the annual rate of change in the absolute CD4 cell count between study arms.

• To compare the annual rate of change in the CD4 cell count percentage between study arms.

• To compare the median log_10 _HIV viral load between study arms.

• To compare the rate of drug-related adverse events between study arms.

• To compare the median frequency of HSV reactivations per year between study arms.

• To compare the rate of acyclovir-resistant HSV between study arms.

• To compare quality of life between study arms.

A substudy will characterize plasma markers of inflammation in this cohort of HAART-naive HIV-infected patients and compare the levels of these markers between study arms.

### Study Hypotheses

The primary hypothesis of the trial is that valacyclovir 500 mg orally twice daily will delay the time until HAART is initiated among adults co-infected by stable untreated HIV and HSV type 2 co-infection. The secondary hypotheses are that valacyclovir 500 mg orally twice daily is associated with a slower rate of change in both the absolute CD4 cell count and the CD4 cell count percentage, a lower median log_10 _HIV viral load, a similar rate of drug-related adverse events, a lower frequency of HSV reactivations, a similar rate of acyclovir-resistant HSV, and improvements in quality of life compared with placebo.

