### Treatment Groups

Participants in the intervention group will receive oral valacyclovir 500 mg twice daily, the standard dose used for HSV-2 suppression in HIV-infected individuals[15,62]. Valacyclovir is safe and well tolerated, as evidenced by clinical trials, where side effects have been reported at rates no different from those of placebo, and clinical experience[54,55,63,64]. Individuals in the control arm will receive an odourless placebo tablet identical to valacyclovir in appearance and taste, to be taken twice daily. Use of other anti-HSV medication (including topical acyclovir) during the trial is prohibited, except during treatment of herpes flares (described below).

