### Management of symptomatic herpes during the trial

If a clinical reactivation of herpes symptoms occurs during the trial, participants are instructed to continue their study drug, present for clinical assessment, have samples taken to attempt microbiologic confirmation of the diagnosis where resources permit, and consider optional open-label treatment. Although participants in the treatment arm may thus receive a total valacyclovir dose of up to 3 g per day for 5 days, this quantity remains well within the safe therapeutic window of this drug. Of note, the occurrence of herpes flares in a study participant does not in itself unblind the study, because a small proportion of individuals taking chronic suppressive anti-HSV medications can experience herpes reactivations. If HSV resistance is suspected, specimens will be tested for acyclovir resistance using a plaque reduction assay[69].

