Nine months is a clinically important difference in the time for HIV-infected patients to delay initiation of lifelong HAART. During this time, patients could avoid the costs, toxicity risks, and resistance risks of ARVs. Because typical HAART regimens can cost $1200 per month compared with only $150 per month for valacyclovir, this strategy could result in an annual net savings of nearly $10000 per patient based on medication costs alone. Further, although the toxicity profile of current ARVs is significantly better than in earlier years of the HIV epidemic, long-term toxicities remain unknown because most of the agents in current use were approved within the last 5-10 years. The ARV resistance risks to be avoided are also considerable; in clinical trials evaluating efavirenz-based HAART regimens, the current 'gold standard' for first-line ARV therapy, 30-70% of the 15-20% patients experiencing virologic failure at one year have evidence of resistance to the NNRTI class of drugs, effectively eliminating the potential for using standard agents in this class thereafter[73-77]. Delaying HAART also provides time for patients to prepare psychologically for starting HAART, which is an important predictor of subsequent adherence[78,79]. Nine months is also the time between 3 quarterly appointments, allowing ample time for clinician and patient to prepare for HAART. Finally, although there is theoretical risk of developing drug-resistant HSV with chronic valacyclovir, this risk is minimal even in immunocompromised patients. Resistance rates have stayed stable at 5-6% despite increasing population exposure to related drugs over 2 decades, perhaps because it imposes a fitness cost on the virus[15,80-83]. Resistant HSV is occasionally seen in advanced HIV patients with persistent lesions despite therapy, not in asymptomatic shedding. For safety, those with frequent recurrences unresponsive to therapy during the trial will have their viral isolates tested for resistance.

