### Secondary Analyses

Random effects models will be used to compare the annual rate of change in the absolute CD4 cell count, the annual rate of change in the CD4 cell count percentage, and the median log_10 _HIV viral load between study arms. The rate of drug-related adverse events per year of follow-up, the number of episodes of HSV reactivations per year occurring at any anatomic site, the proportion of microbiologically confirmed flares of HSV during the trial that are caused by laboratory-confirmed acyclovir-resistant HSV, and the median overall quality of life score [84] at each 6-monthly time point will be compared between groups using Wilcoxon rank sum tests. All analyses will be by intention to treat, meaning that all participants will be analysed in the groups to which they were randomized.

Efforts to ensure that the CD4 and other trial data are well collected include biannual investigator meetings to review study procedures, regular site monitoring visits, and electronic data checks at the CTN National Data Centre. Because the analyses on rates of change in CD4 will only include CD4 counts prior to HAART initiation, the usual problem in HIV clinical trials of missing data among patients doing poorly clinically and dropping out of the trial is not anticipated to be an issue. Patients doing poorly clinically will reach the primary outcome, and it is only their CD4 counts before this time that will be included in the analysis.

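### Two secondary hypotheses claim similar adverse-event and resistance rates, but the only analysis named for them is a test of difference, which cannot support similarity

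*Protocol article*

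**What the plan says.** Study Hypotheses lists the expected secondary results for valacyclovir. Most are directional: slower CD4 change, lower viral load, fewer reactivations, better quality of life. Two are not: "a similar rate of drug-related adverse events, a lower frequency of HSV reactivations, a similar rate of acyclovir-resistant HSV". No margin accompanies either use of the word similar.

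Secondary Analyses names the measures for these two outcomes: "The rate of drug-related adverse events per year of follow-up" and "the proportion of microbiologically confirmed flares of HSV during the trial that are caused by laboratory-confirmed acyclovir-resistant HSV". Together with reactivation frequency and quality of life, they "will be compared between groups using Wilcoxon rank sum tests".

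Three other places bear on what these comparisons can show:
- Treatment Groups reports that in earlier trials "side effects have been reported at rates no different from those of placebo", with no figure.
- The closing part of Sample Size Calculation gives a background for resistance: "Resistance rates have stayed stable at 5-6% despite increasing population exposure to related drugs over 2 decades".
- Management of symptomatic herpes during the trial has participants with a flare "have samples taken to attempt microbiologic confirmation of the diagnosis where resources permit", and adds: "If HSV resistance is suspected, specimens will be tested for acyclovir resistance using a plaque reduction assay".

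The sample size of 240 per arm is derived for the primary endpoint. The article states no power for the adverse-event or resistance comparisons.

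**The concern.** The Wilcoxon test suits the directional hypotheses, where rejecting no difference is evidence for the claim. For the two similarity hypotheses the logic runs the other way. The claim sits on the side of the null hypothesis, and failure to reject it may mean equal rates or too few events. A better-suited test of difference, or a different denominator, would not change that.

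What is at stake is the harm side of the balance. The article says most people with HSV-2 have no symptoms, plans treatment for years, and sets possible harms against a delay of about nine months in starting HAART. It argues that the resistance risk is minimal and that the drug is safe enough for wide use. A conclusion of similar rates would feed directly into that argument, so the analysis should be able to carry it.

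**Working it through.** **Step 1. Hypothesis against test.** For each of the two outcomes the hypothesis is similar rates, the test has a null hypothesis of no difference, and no margin or interval criterion is stated. Rejection refutes the hypothesis; non-rejection leaves it undecided. This follows from the two sections alone and needs no arithmetic. The plan has no power figure of its own to reproduce for these outcomes.

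**Step 2. How often a doubling would go undetected.** Two-sided 0.05 is assumed, because the article states no level for secondary outcomes. With placebo rate p, valacyclovir rate 2p, and n1 and n2 units per arm:

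- power = Φ[(p − 1.96·SE0) / SE1]
- SE0 = √[p̄(1 − p̄)(1/n1 + 1/n2)], where p̄ is the pooled rate
- SE1 = √[p(1 − p)/n1 + 2p(1 − 2p)/n2]

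For a yes/no outcome per unit, a tie-corrected Wilcoxon test is nearly the same as this two-proportion test.

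*Resistance.* The input is 5-6%, read as a rate per confirmed flare, with flares treated as independent. Both are assumptions, and so are the flare counts.

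Example: p = 0.05 and 240 flares per arm give SE0 = 0.02404 and SE1 = 0.02394. Then (0.05 − 1.96 × 0.02404)/0.02394 = 0.12, and Φ(0.12) = 0.55.

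| Confirmed flares, placebo / valacyclovir | Power, 5% vs 10% | Power, 6% vs 12% | Doubling missed |
|---|---|---|---|
| 240 / 240 | 55% | 63% | 37-45% |
| 100 / 100 | 27% | 32% | 68-73% |
| 100 / 30 | 21% | 23% | 77-79% |
| 50 / 50 | 16% | 18% | 82-84% |

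Fisher's exact test at 100 / 30 flares has power 0.17 for 5.5% vs 11% (83% missed) and 0.42 for 5.5% vs 16.5%. Power of 80% for a doubling needs 435 flares per arm at 5% and 356 at 6%.

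To see what a non-significant result would leave open, take 6/100 against 2/30 resistant flares. The ratio is 0.0667/0.06 = 1.11, and the SE of its log is √(1/2 − 1/30 + 1/6 − 1/100) = 0.79. The 95% interval is about 0.24 to 5.2.

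*Adverse events.* The article gives no rate, so the range is shown for 240 participants per arm.

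| Participants affected, placebo vs valacyclovir | Power |
|---|---|
| 1% vs 2% | 15% |
| 3% vs 6% | 35% |
| 5% vs 10% | 55% |
| 8% vs 16% | 77% |
| 10% vs 20% | 87% |
| 20% vs 40% | over 99% |

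Simulating the planned Wilcoxon test on individual yearly rates agrees: about 0.36-0.38 at 3% vs 6%, 0.54-0.56 at 5% vs 10%, 0.86 at 10% vs 20% and 0.99 at 20% vs 40%. With events clustered within participants to varying degrees (overdispersion 0 to 4), power for a doubling is 18-20% from a placebo rate of 0.005 per year, 44-62% from 0.02, 62-94% from 0.05 and 73-100% from 0.10.

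**Step 3. What an interval criterion would need.** With truly equal rates, one-sided 2.5% and 80% power, n per arm = 2p(1 − p)(1.96 + 0.842)²/m². The margins m here only illustrate scale.

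- Resistance at 5%, m = 5 points: 2 × 0.0475 × 7.849/0.0025, or 299 flares per arm; at 6%, 355. With m = 10 points: 75 and 89.
- Adverse events at 10%, m = 10 points: 142 participants per arm; at 20%, 252. With m = 5 points at 10%: 566.

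**The case against.** The strongest reply is that no misreading is written down. A reader might infer that a doubled rate would often be reported as similar. The article contains no such rule: its objectives speak of comparing rates, and the word similar can be read as an expectation of no excess harm. That reply stands. The point is limited to what the named analysis can support.

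Second, margins and interval reporting usually belong in an analysis plan, and this is a condensed article. That is right as far as a missing margin goes, and a missing margin is not the point here. The article itself fixes both the hypothesis and the test, and the two do not fit. Naming a test does not rule out reporting intervals as well, so the repair is easy.

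Third, the magnitudes rest on assumptions. This stands in large part. The flare counts are not in the article. The 5-6% figure has no stated denominator and appears in a passage on immunocompromised patients, whereas participants enter with CD4 counts of 400-900. For adverse events, a reader might generalise from low rates to say that a doubling would often be missed; from 10% of participants upwards the calculation shows the opposite.

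Fourth, both outcomes are secondary, serious adverse events are reviewed by the monitoring committee every six months, and tolerability also rests on earlier placebo-controlled trials. All true. This limits the consequence, but none of it tests similarity in this trial.

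**Conclusion.** The point holds as a mismatch between two stated elements: two hypotheses of similarity, and a test of difference as the only analysis named for them. That conclusion depends on no assumed rate.

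The size differs by outcome. For resistance, information is likely to be thin. Confirmation is attempted only where resources allow, and valacyclovir is expected to reduce flares. If 5-6% applied per confirmed flare, a doubling would be missed in 37-45% of trials even with 240 flares per arm, and in about 77-83% with 100 against 30. For adverse events the size cannot be fixed, because no rate is given: a doubling is often missed at 3-5% of participants and usually found at 10% or more.

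The documents do not support saying that the trial will report doubled rates as similar, or that adverse-event increases would generally be missed. The primary analysis is unaffected. The change is worth making because it costs almost nothing.

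**What to change.** For drug-related adverse events and acyclovir-resistant HSV, replace the p-value as the criterion. Report the between-arm rate difference and rate ratio with two-sided 95% confidence intervals. Then either:

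- state that similarity will be claimed only if the upper limit excludes an excess set in advance by the investigators, before unblinding; or
- reword both hypotheses as estimation and report the largest excess that the data do not exclude.

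Keep the tests of difference for the hypotheses of benefit. For resistance, report the numbers of flares sampled, confirmed and assayed in each arm and allow for repeated flares in one participant. An interval does not repair selective sampling, or assaying only when resistance is suspected.

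The cost is a few sentences and one table from data already being collected, with no extra visits or participants. The downside is that similarity in resistance may not be claimable: even a 5-point margin would need about 299-355 confirmed flares per arm under the assumptions above. For adverse events, 240 per arm would support a 10-point margin up to a rate just under 20%, but not a 5-point margin at a rate of 10%.
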